### Sample size

The primary outcome is the total Aberrant Behaviour Checklist (ABC) score measured repeatedly at six and 12 months following recruitment. The pilot study [15] generated mean baseline ABC scores of 45.4 (SD 26.4). A reduction of 0.45 of a standard deviation on the ABC score in the ABC group compared to the TAU group is considered to be clinically important. Using an analysis of covariance approach based on a correlation of 0.48 between the baseline and post-intervention ABC measurements (as per pilot study, 15) 80 patients per arm will be required to detect a difference of 0.45 SD with 90% power and 5% significance level. Inflating for clustering within the community intellectual disability services, using the formula proposed by Eldridge et al. [31] which accounts for variable cluster sizes and an intracluster correlation of 0.062 (estimated from the pilot study), an average cluster size of 12 (we expect it to be 13, however, allowing for 10% attrition and rounding it up to the nearest integer we have used a cluster size of 12 in our calculations), and a standard deviation for the cluster size of 3, a total of 276 patients will be required. However, this sample size can be reduced as each patient will provide two measurements of ABC score. Using a correlation of 0.6 between the 6 and 12 months post intervention ABC measurements (15,16) and a cluster size of 2, a total of 442 ABC measurements from 221 patients will be required. In performing this calculation we have assumed that there will be no treatment by time period interaction over 12 months supported by the pilot studies [11,12]. To allow for 10% attrition over the 12 month period a total of 246 patients will be recruited to the trial thus requiring 19 clusters. The sample size calculation is based on the program and formulae in STATA version 12.

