### Randomisation

Once the services have been recruited, randomisation will be performed using a web based randomization system which uses random permuted blocks on 1:1 allocation. Although originally we had discounted minimisation given the lack of good evidence for the impact of various variables on patient outcomes, given the variation in cluster sizes we will use the following data in our randomisation planning: team size (number of full time equivalent staff), in or out of London, number of service users registered per team. We have calculated the ratio of staff:patient in and out of London teams and in order to account for the variation we will stratify the teams by a binary factor to indicate whether a team is below or above a median ratio. Randomisation will take place after the participants have been screened for eligibility and consented to the trial. Baseline data collection will follow.

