### Statistical analysis

We shall follow CONSORT guidelines for the analysis of cluster randomised trials and reporting of findings (http://www.consort-statement.org/).

The baseline characteristics of the PBS and TAU groups will be summarised using means, standard deviation and proportions as appropriate. A three level regression model adjusting for baseline ABC measurements, time period and effects of clustering by services and accounting for repeated measures within subjects will be used for the primary analysis. Similar analyses will be conducted for the secondary outcomes using appropriate regression models depending on the type of outcome. Results from all secondary analyses will be presented as estimates with confidence intervals and treated as exploratory. If we encounter missing data, bias due to missing data will be investigated initially by comparing the characteristics of the trial participants with complete follow-up measurements and those who have incomplete follow-up or no outcome data, descriptively. If differences are observed in the participants’ characteristics in the descriptive analysis, factors which are likely to be associated with the outcome will be included in a multilevel logistic regression analysis (with missing yes or no as outcome) to identify predictors of missing data. If predictors associated with both missing data and the outcomes are found, these will be included in the multilevel models examining the effects of intervention on the outcomes [45]. A sensitivity analysis will also be carried out to examine the effect of PBS on ABC score after adjusting for area deprivation and the service staff to patient ratio if appropriate. Multiple imputation may be used as part of the sensitivity analysis accounting for the clustered nature of the data if considered appropriate [46-48]. As part of the sensitivity analysis we will also examine intervention by time period interaction. All analyses will be carried out on an intention to treat basis. A detailed statistical analysis plan will be agreed by the Trial Steering Committee prior to the analysis of unblinded data.

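### The randomisation stratum (staff-to-patient ratio) is left out of the primary model, so if the ratio is prognostic the standard error is too wide and the test conservative

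*Protocol article*

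**What the plan says.** Under Randomisation, the web-based system "uses random permuted blocks on 1:1 allocation", and "we will stratify the teams by a binary factor to indicate whether a team is below or above a median ratio". The same section says that minimisation had at first been discounted because of the "lack of good evidence for the impact of various variables on patient outcomes". Team size, location in or out of London and number of registered users were then brought into the planning because cluster sizes vary.

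Under Statistical analysis, the primary analysis is "A three level regression model adjusting for baseline ABC measurements, time period and effects of clustering by services", with repeated measures within subjects also accounted for. The stratification factor is not in that list. Later in the same section a sensitivity analysis estimates the effect of PBS on ABC "after adjusting for area deprivation and the service staff to patient ratio if appropriate". Secondary outcomes are to be analysed in a similar way, so the omission carries over to them.

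**The concern.** Stratified allocation makes the arms alike on the stratum, so the stratum contributes little or nothing to the chance difference between arms. A model without the stratum does not know this. It leaves the stratum's variance in the between-team residual and reports a standard error for a design in which that variance could have fallen unevenly. The interval is then wider than it should be, the test rejects too rarely, and much of the benefit of stratifying is not collected.

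This is not a detail that the article leaves open. It names the primary covariates and places the stratifying variable elsewhere, conditionally. That also leaves a discretionary choice over a variable which the design itself has fixed. With 19 teams, between-team variance is a large part of the error of a team mean (about half, as shown in the working), so the point is not negligible by construction.

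**Working it through.** **Inputs (Sample size section).** Effect 0.45 SD, 90% power, 5% level, baseline correlation 0.48 ("a correlation of 0.48 between the baseline and post-intervention ABC measurements"), ICC 0.062, mean analysed cluster size 12 with SD 3, correlation 0.6 between the two follow-ups, 10% attrition.

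**The plan's own figures reproduce.**
- ANCOVA: 103.78 × (1 − 0.48²) = 103.78 × 0.7696 = 79.9, so 80 per arm.
- Design effect: 1 + [((3/12)² + 1) × 12 − 1] × 0.062 = 1.7285; 160 × 1.7285 = 276.6 (stated 276).
- Two visits: 276 × (1 + 0.6)/2 = 220.8, so 221 patients.
- Attrition: 221/0.9 = 245.6, so 246; 246/13 = 18.9, so 19 clusters.

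No step uses the stratum, so the stated N does not depend on this point.

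**Variance of a team mean (SD units, averaged visits).**
- Between teams: 0.062 × 0.7696 = 0.0477.
- Within teams: 0.938 × 0.7696 × 0.8/12 = 0.0481.
- Between-team share: 0.0477/0.0958, about 50%.

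**Reported against true standard error.** Take 20 equal teams in two balanced strata, and let the stratum explain a share *s* of the between-team variance.
- True variance of the estimate, with or without the term: (4/20) × [0.0477(1 − *s*) + 0.0481].
- Expected variance reported without the term: (4/20) × [0.0477(1 − *s*) + 0.0481 + (20/18) × 0.0477*s*].
- At *s* = 25%: true SD = √(0.2 × 0.0839) = 0.130; reported about √(0.2 × 0.0972) = 0.139.
- Simulated mean SE against true SD: 0.137 against 0.129 at 25% (about 6% too wide), and 0.139 against 0.120 at 50% (about 15% too wide). The true SD was the same with and without the term at every share.

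**Simulated test, 20 equal teams** (cluster means, t reference, 20,000 runs per setting; the shares are assumptions):

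| Share explained | Type I without / with term | Power without / with term |
|---|---|---|
| 0% | 4.9% / 5.0% | 87.0% / 86.8% |
| 10% | 4.6% / 5.1% | 87.3% / 88.3% |
| 25% | 3.5% / 4.9% | 88.3% / 90.7% |
| 50% | 2.4% / 5.2% | 89.4% / 94.5% |

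**Simulated test, 19 unequal teams** (mean size 12, SD 3; blocks of 4 assumed, some incomplete; otherwise as above):

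| Share explained | Type I without / with term | Power without / with term |
|---|---|---|
| 0% | 4.9% / 4.9% | 83.2% / 82.9% |
| 20% | 4.0% / 5.0% | 84.2% / 86.5% |
| 40% | 3.3% / 5.3% | 84.8% / 89.9% |
| 60% | 2.2% / 4.9% | 85.6% / 92.9% |

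A further run with 20 balanced teams (40,000 runs) gave type I error without the term of about 4.5%, 4.0%, 2.9% and 2.0% at shares of 10%, 20%, 40% and 60%. Unequal teams and incomplete blocks do not remove the effect. What bears on this point is the difference within each row, not the absolute level of power.

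**The case against.** The strongest reply is about size, and most of it stands.

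- **True variance.** A reader might infer that adjustment makes the treatment estimate itself less variable, by 10%, 20% or 30% at shares of 20%, 40% or 60%. It does not: balanced stratification has already removed that component, and only the reported standard error changes. Unadjusted power therefore also rises as the stratum becomes more prognostic. The gains at those shares are about 2.5, 5 and 7 points, smaller than a fixed unadjusted baseline would suggest.
- **Plausible shares.** A median split captures at most 2/π, about 64%, of the variance carried linearly by a normally distributed ratio. Shares of 20%, 40% and 60% would then need the ratio to explain about 31%, 63% and 94% of between-team variance, after baseline ABC has absorbed part of it. The last is not credible.
- **Motive.** A reader might infer that the sponsor stratified because the ratio was believed to predict outcome. The Randomisation section says the opposite about the evidence and gives variation in cluster size as its reason.
- **Reference distribution.** The article states none. With a normal reference, the same kind of simulation gives type I error of about 5.3% without the term and 6.8% with it at a 20% share. The conservatism described here is conditional on a t reference.
- **Consequence.** The error is in the safe direction, the sample size claims no gain from stratifying, and a detailed analysis plan is still to be agreed.

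None of this removes the mismatch. The article specifies the primary covariates and makes adjustment for the ratio optional, so a later plan would have to change the stated analysis rather than fill a gap.

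**Conclusion.** The point holds as a mismatch between design and primary analysis with a conservative consequence. If the stratum is prognostic, the reported standard error is too wide. For assumed shares of 10% to 60% of between-team variance, type I error falls to between about 4.5% and 2%, and the adjusted model gains between about 1 and 7 points of power. If the stratum is not prognostic, nothing is lost by omitting it, and including it costs about 0.3 points. These sizes rest on an unevidenced prognostic effect, on a t reference and on cluster means standing in for the full three-level model. The lower end of the range is the more plausible.

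A reader might go further and infer bias, excess false positives or a sample size that is too small because of the omission. The documents support none of these. It is a low-cost improvement that should be made, because the cost of including the term is close to nil and the possible gain is several points of power with a correctly sized test.

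**What to change.** Add the binary stratification factor (ratio below or above the median, as used in the allocation) as a prespecified fixed effect in the primary three-level model and in the matching models for secondary outcomes, without any condition. Keep area deprivation and the continuous staff-to-patient ratio as sensitivity adjustments. State the reference distribution alongside; the type I error and power figures given here apply to a t reference on between-team degrees of freedom.

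The cost is one model term and one between-team degree of freedom. The sample size does not change. The change can be made in the detailed statistical analysis plan, which the article says will be agreed by the Trial Steering Committee before unblinded data are analysed.

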### Health economic evaluation

Analyses will be conducted from a health services perspective and from a societal perspective. The cost-effectiveness measure will be the incremental cost per QALY gained of PBS versus treatment as usual. This will be calculated as the mean cost difference between PBS and treatment as usual divided by the mean QALY difference to give the incremental cost-effectiveness ratio (ICER). This will allow for resource allocation decisions across different health services. However, as there is no evidence of the relationship between challenging behaviour and QALYs, we will also calculate the cost per point change in the primary outcome measure, (ABC). Unit costs will be taken from standard published sources such as the Office for National Statistics and Personal Social Services Research Unit (PSSRU). The cost of PBS will also include staff resources, supervision and training. Additional information on hospital admissions and out-of-area transfers will be collected to ensure costings of the secondary care component for both trial arms are robust. Predetermined values will be used [49,50] to calculate the area under the curve using time-weighted averages of utility scores collected at baseline and each follow up point. As baseline utility scores are not controlled for prior to randomisation, utility scores may differ between trial arms at baseline. Thus, regression analysis will be used to control for differences in baseline utility scores. We will use non-parametric methods for calculating confidence intervals around the ICER based on bootstrapped estimates of the mean cost and QALY differences. The bootstrap replications will also be used to construct a cost-effectiveness [51] acceptability curve, which will show the probability that PBS is cost-effective compared to standard care at 12 months for different values of the willingness of the NHS to pay for an additional QALY. We will also subject the results to extensive deterministic (one-, two- and multi-way) sensitivity analyses.

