### The financial burden of challenging behaviour

European data on the cost of disorders of the brain [15] estimate that the cost of intellectual disabilities is 43bn euros most of which is accounted for by costs of direct health and non-medical care. A survey of five London areas showed that 67% (£14 million, 2004–2005 prices) of combined medical and social care budgets supported 134 out-of-area placements for adults with intellectual disability and challenging behaviour [16]. Individual care packages commonly ranged from £100 k to 450 k per annum. Other studies indicate that costs are higher for people with more severe intellectual disability and those with greater levels of challenging behaviour, with specialist accommodation accounting for the majority of the cost [17-19].

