### PBS based staff training

Specific staff competencies are a crucial factor in maintaining improvements in behaviour. However, given the resource associated with delivering PBS, only about half of service users in need of PBS may be treated at any time [24]. Lack of competencies in managing challenging behaviour is also an important factor in perpetuating out-of-area placements [25,26]. Even where there are tertiary specialist teams which provide ABA/PBS, service users often have to wait several months to receive help.

One approach to meeting this shortfall is to train paid carers and professional staff in PBS. McClean et al. [24] and Grey & McClean [27] have reported descriptive data on training 132 paid carers in a non randomised clinical study (n = 60) that reported significant reductions in challenging behaviour in people in the target group compared with controls. However, the instrument used to measure the primary outcome does not have established psychometric properties, the study was uncontrolled and included training paid carers (rather than professionals), who are likely to require a different set of skills and knowledge from the outset. The authors estimated that PBS based training may lead to savings of £2 K per person treated.

The central objective of good practice in treating challenging behaviour is maintain individuals who present with such behaviours locally and to avoid transfers to out-of-area facilities [28]. Other guidance advocates a person centred approach encompassing tenets of PBS which leads to environments capable to deal with such behaviour and the implementation of skilled commissioning for care provision [29].

We argue that a rigorous evaluation of the clinical and cost effectiveness of PBS delivered by appropriately trained staff is long overdue. The focus of this project is highly relevant given the widespread implementation of PBS and thus the findings would have significant practice and policy benefits internationally. Moreover, the economic analysis will determine whether the intervention incurs costs beyond and above treatment as usual and any reductions in challenging behaviour are associated with reduced use or resources and improved quality of life.

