#### Secondary outcome measures

Mental health and autism spectrum disorders will be assessed by the mini version of the Psychopathology Assessment Scale for Adults with Developmental Disability (mini PASADD) [38]. It is administered by trained professionals to family and/or paid carers and to the service user where possible. The instrument comprises 86 psychiatric symptoms with threshold scores for the following psychiatric disorders: Depressive Disorder, Anxiety Disorder, Hypomania/Mania or Expansive mood, Obsessive Compulsive disorder, Psychosis, Dementia or Unspecified Disorder and a screen for pervasive developmental disorder. The latter will be administered once at baseline.

EuroQol Youth (EQ-5D-Y) will be used to calculate Quality Adjusted Life Years (QALYs) in line with accepted guidance [39]. The EQ-5D-Y is a 5 domain (usual activity, self-care, mobility, pain and anxiety/depression), 3 level (no problems, some problems and extreme problems) questionnaire. It will be administered at all time points.

Community participation will be assessed with the Guernsey Community Participation and Leisure Activities Scale (GCPLAS) [40]. It was developed to monitor the impact of interventions on the service user’s daily living. It contains six categories of activity that refer to 49 operationally defined contacts. The frequency of participation over the previous six month period is rated on a five point scale. It will be administered at all time points.

Family carer burden will be measured by the Uplift/Burden Scale [41], a 23-item scale that has six uplift and 17 burden items. The scale has previously been used in this population (6). It will be administered at all time points.

Family carer psychiatric morbidity will be measured by the GHQ12 [42].

Paid carer burden will be measured by the Caregiving Difficulty Scale-Intellectual Disability (CDS-ID) [43]. It is adapted from an existing scale and measures subjective burden. It will be administered at all time points.

Costs of care will be collected using a modified version of Client Services Receipt Inventory (CSRI) for people with intellectual disability [44]. It will be administered at all time points for the preceding 6 months.

Use and/or change of all medications will be recorded during the study period.

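### The economic evaluation commits to baseline adjustment for utility but states none for cost, although six-month cost is collected at baseline

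*Protocol article*

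**What the plan says.** All references are to the protocol article.

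- **Health economic evaluation** defines the ICER: "This will be calculated as the mean cost difference between PBS and treatment as usual divided by the mean QALY difference". Confidence intervals and the acceptability curve come from bootstrapped mean cost and QALY differences. Two perspectives are planned, health services and societal.
- The same section gives a reason for adjusting one of the two terms: "As baseline utility scores are not controlled for prior to randomisation, utility scores may differ between trial arms at baseline". It concludes that "regression analysis will be used to control for differences in baseline utility scores". Nothing comparable is said about cost.
- **Secondary outcome measures** lists the modified CSRI as the cost instrument: "It will be administered at all time points for the preceding 6 months". Cost for the six months before baseline will therefore be on file.
- **Randomisation** stratifies teams by whether their staff-to-patient ratio is above or below the median. Cost is not a factor.
- **Statistical analysis** gives secondary outcomes models similar to the primary one, which adjusts for baseline and for clustering by service. It does not mention the ICER.

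**The concern.** The reason given for adjusting utility is that the randomisation does not balance it. That holds equally for cost, yet only utility receives a stated adjustment. An analyst following the section as written could divide an unadjusted cost difference by an adjusted QALY difference.

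Comparing costs of care is the first secondary objective. The background section reports that "costs are higher for people with more severe intellectual disability and those with greater levels of challenging behaviour". Both characteristics exist before the trial starts and could differ between arms by chance when only 19 teams are randomised. If pre-trial cost predicts later cost, leaving it out discards precision and lets a chance baseline difference pass into the ICER numerator.

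**Working it through.** **The plan's own figures.** The article gives no economic figure to reproduce. The number of teams comes from the sample size section, which reproduces at each step:

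- Per arm: 103.8 × (1 − 0.48²) = 79.9, so 80.
- Design effect: 1 + [(1 + (3/12)²) × 12 − 1] × 0.062 = 1.7285; 160 × 1.7285 = 276.6 (stated 276).
- Two follow-up measures: 276 × (1 + 0.6)/2 = 220.8, so 221.
- Attrition: 221/0.9 = 245.6, so 246. Clusters: 246/13 = 18.9, so 19.

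**Does the general rule already cover cost?** The CSRI is listed under Secondary outcome measures, so the rule could be read to include it. The EQ-5D-Y is listed there too, and the economic section still gave utility its own adjustment. If the rule governed the economic inputs, that sentence would be unnecessary. The ICER numerator is therefore left ambiguous.

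**Gain from adjusting.** With baseline cost as a covariate, the standard error is multiplied by √(1 − r²), where r is the correlation between baseline and follow-up cost (assumed):

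- r = 0.5: √0.75 = 0.866, 13% lower.
- r = 0.7: √0.51 = 0.714, 29% lower.
- r = 0.9: √0.19 = 0.436, 56% lower.

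**Illustration in pounds.** None of these cost inputs is given for the trial population. Assumptions: annual cost SD of £25k, £50k or £87.5k (the last is (£450k − £100k)/4), and a cost intracluster correlation of 0.062, borrowed from the Aberrant Behaviour Checklist (ABC). With 9 and 10 teams, the arms hold 246 × 9/19 = 116.5 and 246 × 10/19 = 129.5 people. Mean cluster size is 246/19 = 12.95.

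Design effect = 1 + [(1 + 0.25²) × 12.95 − 1] × 0.062 = 1.791.

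SE = SD × √[1.791 × (1/116.5 + 1/129.5)] = SD × 0.1709.

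| SD | Unadjusted SE | r = 0.5 | r = 0.7 | r = 0.9 |
|---|---|---|---|---|
| £25k | £4.27k | £3.70k | £3.05k | £1.86k |
| £50k | £8.54k | £7.40k | £6.10k | £3.72k |
| £87.5k | £14.95k | £12.95k | £10.68k | £6.52k |

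On the same assumptions, the 95% chance range of the between-arm difference in annual baseline cost is 1.96 × SE: about ±£8.4k, ±£16.7k and ±£29.3k.

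**Simulation.** 3,000 trials per setting, with the same correlation at team and individual level, agree. At SD £25k the adjusted estimates had SDs of £3.61k, £3.00k and £1.81k. Across all settings, with no true effect, the average of both estimators was within £0.25k of zero, so neither is biased.

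**The case against.** **The plan does not say raw.** A reader might infer that the authors chose an unadjusted cost difference. The text does not say so. It uses the same mean-difference wording for QALYs and then adjusts those, and an analysis plan that is not shown may specify the cost model. This stands, so the point is limited to what the section commits to and what it leaves unstated.

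**Utility has an extra reason for adjustment.** By the trapezoid rule at 0, 6 and 12 months, baseline utility carries a quarter of the QALY (0.25, 0.50, 0.25), so imbalance enters the outcome directly. Baseline CSRI cost is not part of follow-up cost. This also stands, and the case for cost should not be called stronger. But the reason the section itself gives is lack of control at randomisation, and that covers both.

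**Chance imbalance is not confounding.** A reader might conclude that the cost effect would be biased. Randomisation does not support that: the unadjusted estimator is unbiased, and the loss is precision and possible imbalance in the one trial that is run.

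**The pound figures are borrowed.** It is tempting to set a few expensive placements against the quoted saving. For example, three extra people at £200k above average among 123 shift the mean by 3 × £200,000/123 = £4,878, compared with "PBS based training may lead to savings of £2 K per person treated". The documents do not support that as a forecast. The statement that "Individual care packages commonly ranged from £100 k to 450 k per annum" follows a survey of out-of-area placements in five London areas. The training is aimed at people without the most complex behaviours. The saving comes from a non-randomised study of paid carers that the article itself criticises. Nor do the documents show that such packages enter the health-service perspective.

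**Conclusion.** The point holds as a gap in the stated estimator. Baseline adjustment is promised for one term of the ICER and not the other, although the stated reason fits both and the covariate is collected. The rule for secondary outcomes does not clearly close the gap.

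The cost of leaving it is precision: a standard error that adjustment would lower by about 13% at r = 0.5 and 56% at r = 0.9. Those percentages depend only on r, which is assumed, and on the correlation being similar at individual and team level. The pound amounts also depend on an assumed SD and intracluster correlation and serve only as illustration.

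The gain further assumes that the baseline cost window is unaffected by allocation. The article places baseline data collection after randomisation, so this needs confirming. The same applies to baseline utility.

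This is a free improvement. It does not show that the planned cost comparison is biased.

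**What to change.** Add to the Health economic evaluation section that:

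1. In each perspective, incremental cost is estimated by regression on arm, with baseline six-month CSRI cost (same perspective) and the stratification factor as covariates, allowing for clustering by service.
2. This adjusted cost difference, together with the QALY difference adjusted for baseline utility, is computed in every bootstrap replicate and used for the ICER and the acceptability curve.
3. The baseline CSRI period ends before any intervention begins.

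If the rule for secondary outcomes was meant to cover the ICER, say so there. The cost is a few sentences in the plan; no new data, visits or participants are needed.

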## Methods

### Trial design

Multicentre cluster researcher-masked randomised controlled trial of manualised PBS-based staff training programme for managing challenging behaviour in adults with intellectual disability. The control group will receive treatment as usual. Treatment as usual will also be available to the participants in the intervention arm. The unit of randomisation will be the community intellectual disability service. A cluster randomised design is considered appropriate in the light of this being an educational intervention aimed at groups of professionals and the service [30].

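### The bootstrap for the ICER interval and acceptability curve has no stated service level although services are randomised, and an interval on the ICER is hard to interpret if the QALY difference is near zero

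*Protocol article*

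**What the plan says.** Under Trial design: "The unit of randomisation will be the community intellectual disability service". Under Statistical analysis, the primary model is a three level regression that allows for "effects of clustering by services and accounting for repeated measures within subjects". The same section promises similar regression analyses for secondary outcomes, and says that any multiple imputation would respect the clustering.

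The Health economic evaluation section sets out its own method. The ICER is the mean cost difference divided by the mean QALY difference, with regression used to adjust for baseline utility. For uncertainty it says: "We will use non-parametric methods for calculating confidence intervals around the ICER based on bootstrapped estimates of the mean cost and QALY differences". It continues: "The bootstrap replications will also be used to construct a cost-effectiveness [51] acceptability curve". Cost per point of ABC change is added "as there is no evidence of the relationship between challenging behaviour and QALYs". Deterministic sensitivity analyses follow. None of these steps mentions services or clustering, and nothing is said about the ICER interval if the QALY difference is close to zero.

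**The concern.** There are two separate issues.

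**Clustering.** The article carries the service level through the sample size, the primary model and imputation, but not into the bootstrap. Someone who followed the economic section as worded could resample patients within arm, which treats 246 people in 19 services as independent. Some clustering of costs is to be expected. The cost of PBS includes training and supervision, two professionals are trained per team, and the Treatment as usual section accepts that resources may vary. Any clustering that the bootstrap ignores makes the interval too narrow and moves the acceptability probabilities too far from one half.

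**The ratio.** The article commits to an interval on the ICER and also says it has no evidence linking behaviour to QALYs, so a small QALY difference is possible. When the denominator can change sign, a negative ratio may mean that PBS is cheaper and better or that it is dearer and worse. An interval on the ratio scale cannot tell these apart.

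Cost-effectiveness is part of the study aim in the Abstract, and the ICER is meant to inform resource allocation.

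**Working it through.** **Inputs (Sample size section).** Difference 0.45 SD; 90% power; 5% significance, taken as two-sided; "a correlation of 0.48 between the baseline and post-intervention ABC measurements"; ABC intracluster correlation 0.062; mean cluster size 12 analysed (13 recruited) with SD 3; correlation 0.6 between 6 and 12 months; 10% attrition. No intracluster correlation is given for costs or QALYs.

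**Step 1. Reproduce the plan's figures.**
- Per arm: 2 × ((1.960 + 1.282)/0.45)² × (1 − 0.48²) = 103.8 × 0.7696 = 79.9. The article says "80 patients per arm will be required to detect a difference of 0.45 SD with 90% power and 5% significance level".
- Design effect (DE) for variable cluster size: CV = 3/12 = 0.25, so DE = 1 + ((0.25² + 1) × 12 − 1) × 0.062 = 1 + 11.75 × 0.062 = 1.7285.
- 160 × 1.7285 = 276.6, or 276.2 with a finite-cluster correction to the CV (stated 276).
- 276 × (1 + 0.6)/2 = 220.8 (stated 221); 221/0.9 = 245.6 (stated 246); 246/13 = 18.9 (stated 19 clusters).

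The chain reproduces, so 1.73 is the article's own design effect for ABC.

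**Step 2. What patient-level resampling would do.** The standard error (SE) is too small by the factor 1/√DE. Normal-approximation coverage of a nominal 95% interval for a mean difference is 2Φ(1.96/√DE) − 1.

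| Assumed ICC | DE | True SE / patient-level SE | SE too small by | Coverage |
|---|---|---|---|---|
| 0 | 1.00 | 1.00 | 0% | 95.0% |
| 0.01 | 1.12 | 1.06 | 5% | 93.6% |
| 0.05 | 1.59 | 1.26 | 21% | 88.0% |
| 0.062 | 1.73 | 1.31 | 24% | 86.4% |
| 0.10 | 2.17 | 1.47 | 32% | 81.6% |
| 0.20 | 3.35 | 1.83 | 45% | 71.6% |

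For the acceptability curve, the true probability is Φ(Φ⁻¹(p)/√DE). At DE = 1.7285, a reported 0.95 corresponds to about 0.90, and a reported 0.90 to about 0.84.

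**Step 3. Simulation.** With 10 and 9 teams, sizes about N(12, 3), 3,000 trials and 400 resamples each, patient resampling at ICC 0.062 covered 85%. Plain resampling of whole teams covered about 91% at every ICC tried (0 to 0.20). It removes the dependence on the ICC but still falls short of 95% with so few teams.

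**Step 4. The ratio.** This illustration takes a true cost difference of 1 SE, independent errors, and percentile limits of the ratio in units of cost SE over QALY SE.

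| True QALY difference (in SE) | Replicates with negative QALY difference | 2.5% and 97.5% limits |
|---|---|---|
| 0 | 50% | −18 to 18 |
| 1 | 16% | −10 to 12 |
| 1.96 | 2.5% | −1.3 to 4.1 |
| 3 | 0.1% | −0.4 to 1.5 |

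The limits settle only when the QALY difference is well away from zero. Near zero they are very wide and mix opposite conclusions. The acceptability curve uses the joint cost and QALY differences at each willingness to pay, not the ratio, so it is unaffected.

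**The case against.** The strongest reply is that the article does not name the resampling unit. It nowhere says that patients are resampled, and a fuller plan, which the article says will be agreed before unblinded analysis, may settle it. The article also commits to CONSORT guidance for cluster trials and to similar analyses for secondary outcomes, and it lists EQ-5D-Y and service-use costs among the secondary measures. This stands in part: the conclusion has to be conditional. It does not dispose of the point. The promise of similar analyses concerns regression models, and a multilevel model for EQ-5D-Y would not determine how the bootstrap replications are drawn. Clustering is named even for imputation, so its absence from an inferential method set out in this detail is worth correcting.

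On the ratio, the article says non-parametric methods, not percentile limits, and its acceptability curve stays interpretable near a zero QALY difference. Lack of evidence of a link to QALYs is also not a prediction of no difference. All of this is fair. The commitment to an interval on the ICER remains, without any rule for a denominator that changes sign.

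Four stronger readings are tempting, and the document does not support them:
- That uncertainty will be understated. The unit is unstated, so this holds only if patients are resampled.
- That a near-zero QALY difference makes the interval too narrow. It makes it uninterpretable.
- That ratio instability distorts the acceptability curve. It does not.
- That costs cluster at least as strongly as ABC. No figure supports this.

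The stakes should also be kept in proportion. Costs are a secondary objective, and secondary analyses are to be treated as exploratory.

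**Conclusion.** The point holds in conditional form. As worded, the economic bootstrap has no service level in a trial that randomises services. If patients are resampled and costs and QALYs cluster as ABC does, the standard error is about 24% too small and 95% intervals cover about 86%. Over assumed correlations from 0.01 to 0.10 the coverage runs from about 94% to 82%, and with no clustering there is no loss. These figures rest on a borrowed correlation and a normal approximation, which the simulation supports (85% against 86%).

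The ICER interval is a separate weakness that does not depend on the resampling unit. It arises only if the QALY difference is small relative to its standard error, and its effect is loss of meaning, not false precision. The primary ABC analysis is not affected by either issue.

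**What to change.** In the Health economic evaluation section, or the health economics analysis plan:

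1. State that the bootstrap respects services within arm (two-stage, with shrinkage), with a small-sample correction for about 9 to 10 teams per arm. The alternative is a bivariate multilevel model for costs and QALYs with service as a level.
2. Use the same method for the acceptability curve and for cost per ABC point.
3. Report incremental net monetary benefit with its interval at stated thresholds, plus the cost-effectiveness plane, in place of relying on an interval for the ICER. The ICER can still be given as a point estimate.

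The cost is a few sentences and modest programming, with no new data. Intervals will be wider. With so few teams coverage will remain approximate: plain whole-team resampling reached only about 91% in the simulation, which is why the correction or the model is needed.
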